### Stakeholder education

Prior to implementation of the reports, each ICU will receive education strategies specifically tailored to their site. The education strategies will be informed by local acute KRT leaders, champions, and stakeholders and will serve to identify barriers and facilitators to the program (Table 3). Initial education strategies will likely contain similar themes across all sites and will be managed by our study team, however after receiving feedback through the KPI reports, each site will be encouraged to facilitate and conduct their own audit and educational activities to address any unit specific shortcomings identified in their acute KRT KPI performance.

**Table 3 Tab3:** Components of the multi-faceted intervention and knowledge implementation strategy

Strategy	Description
Education	• Site grand rounds and inter-professional seminars • Monthly video/teleconferencing sessions • Site specific educational sessions by inter-professional content experts and local champions • Provide a summary of current guidelines and best practice • Development of website for repository of evidence supporting implementation including banked webinar of project • In-person or virtual visits with ICU leadership, champions and investigator teams
Coaching	• Provide ongoing resources for interpretation of KPI reports • Common troubleshooting advice cards • Provide clinical decision support resources
Audit and Feedback	• Baseline and monthly reports of process of care indicators of implementation of the intervention • Comparative performance relative to peer ICUs across province • Quarterly video/teleconferencing sessions to discuss provincial KPI reports
Reminders	• Promotional items (posters; bulletins) • Weekly electronic communication to local site champions to ensure ongoing review of KPI reports and access to additional resources

Select outlying prescribers will be contacted by the study team to further evaluate either well performing or poorly performing prescriber patterns as they relate to most recent evidence.

### Primary outcomes

Measurement of change across acute KRT KPIs that will include the following:∘ CKRT: 1) filter life, 2) downtime, 3) delivered dose, 4) ultrafiltration realized and 5) number of access alarms∘ IKRT: 1) treatment completion, 2) delivered dose, 3) solute clearance, 4) ultrafiltration realized and 5) catheter malfunctionNumber of appropriate acute KRT initiationsNumber of patients entering maintenance KRT programsAcute KRT and healthcare systems costs

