**Fig. 2 Fig2:**
[figure not shown]
Outline of learning health system knowledge to action framework. The healthcare system data are used to set local priorities for improvement. Data on priority problems and potential contributors help find the evidence based solutions to improve local health systems (data to knowledge). Using evidence based knowledge, this will inform local quality improvement and implementation science guided efforts (knowledge to performance). Finally, the continuous monitoring of local KPIs and practices will develop practice based knowledge while revealing future opportunities for quality improvement (performance to data). Adapted from Kilbourne et al. [16]

Dialyzing Wisely will utilize a structure-process-outcome framework for quality assessment by implementing a standardized framework to each acute KRT program (Fig. 3) [17, 18]. Each participating ICU will be structured to be led by a team with expertise in KRT (e.g., physician, educator, registered nurse, administrator) who will undergo and further disseminate targeted education strategies prior and during the intervention. Each ICU will receive quarterly performance reports on a minimum suite of essential KPIs tailored to their unit’s specific practice. Through this feedback the team members will work on adjusting and improving KRT practices that do not meet KPI benchmarks. Further, acute KRT prescribers will receive individualized reports outlining their prescription practices and their alignment with best evidence. Follow up with individual ICUs and practitioners will occur to better understand and evaluate prescribing practices. After completion of the intervention period, the impact of the intervention will be measured through select clinical and economic outcome measures (e.g., mortality, lengths of stay, KRT utilization and renal recovery). At this time, using our partners (outlined below) we will transition ownership to local stakeholders.

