#### Monitoring and reporting of acute KRT KPIs

The monitoring, reporting and audit of acute KRT KPIs will be done by means of automatically generated reports delivered directly to KRT stakeholders at each ICU at quarterly intervals (Table 2). These unit-level aggregate summaries of KPIs will be benchmarked to other ICUs in Alberta and will be delivered in an electronic fashion. KPIs captured in the reports for CKRT will include: 1) filter life, 2) downtime, 3) delivered dose, 4) ultrafiltration realized and 5) number of access alarms; and for IKRT: 1) treatment completion, 2) delivered dose, 3) solute clearance, 4) ultrafiltration realized and 5) catheter malfunction.

**Table 2 Tab2:** Intervention definitions and parameters - Key Performance Indicators (KPIs)

**CRRT KPI**	**Operational Definition**	**Proposed Benchmark**
Filter Life	Average number of hours of filter life of all filters per quarter	> 50% of filters last 72 hours
Downtime	Time CRRT not running per day/ Each day of CRRT prescription	< 15%
Delivered Dose	Actual delivered dose in ml/Kg/h / Prescribed dose in ml/Kg/h	> 85% of dose and between 25 and 30 ml/Kg/h
Ultrafiltration Realized	Ultrafiltration realized per 24 hours/ Ultrafiltration prescribed per 24 hours	> 85%
Access Alarms	Number of alarms recorded per machine per day of therapy	< 5 alarms/d
**IRRT KPI**	**Operational Definition**	**Proposed Benchmark**
Treatment Completion	Number of IRRT treatment completed/ Total number of IRRT treatments	100%
Treatment Time	[Delivered – Prescribed hours of dialysis therapy]/ Prescribed hours of dialysis therapy	> 85% of time
Solute Clearance	Percentage difference between serum urea pre-treatment and serum urea post treatment	> 10% decrease/treatment
Ultrafiltration Realized	Ultrafiltration realized for treatment/ Ultrafiltration prescribed per treatment	> 85%
Catheter Malfunction	Number of IRRT runs with catheters reversed/ Number of IRRT runs	< 20%

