APACHE II Score	number
SOFA score	number
Invasive/non-invasive ventilation	hrs/min
Vasopressors (include type)	hrs/min
CRRT/IHD/SLED	hrs/min
Cumulative daily fluid balance prior to RRT	mls
Creatinine, urea, pH, bicarbonate, potassium on day of RRT initiation	result
Renal Recovery at ICU Discharge	y/n - IHD
Renal Recovery at Hospital Discharge	y/n – IHD/PD
Renal Recovery at 6 Months	y/n - IHD/PD
ICU Mortality	A/D
Hospital Mortality	A/D
6-month Mortality	A/D
ICU length of Stay	days
Hospital Length of Stay	days
Number of admissions to site	aggregate
Patient days	aggregate
Ventilator days	aggregate
RRT days	Days CRRT/IHD/SLED
CRRT and IRRT data - filter life, reasons for retiring filters, treatment time lost, prescription/dose, machine alarms, machine down times, type of coagulation, blood flow rates, filtration fraction, adverse events, solute clearance, ultrafiltration realized	aggregate
Economic data - cost of filters, fluids, anticoagulation medications, RRT catheters, patient life-years gained, quality of life adjusted years (QUALY), re-hospitalizations, recurrence/chronic RRT, health care provider related costs	aggregate
QOL and PROMs	aggregate

Data sources will include multiple Alberta Health Services administrative databases, the Nephrology Information System (NIS) and the Patient Based Renal Information System (PARIS) (Supplementary Table 1) [20, 21].

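### The second IKRT primary KPI is named delivered dose in the text, but Table 2 defines treatment time in its place and has no IRRT dose row

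*Protocol article*

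**What the plan says.** The Primary outcomes section of the protocol article lists five KPIs for continuous and five for intermittent therapy. The intermittent list begins "IKRT: 1) treatment completion, 2) delivered dose, 3) solute clearance". The section on monitoring and reporting of acute KRT KPIs gives the same five intermittent items in the same order for the quarterly unit reports: "1) treatment completion, 2) delivered dose, 3) solute clearance, 4) ultrafiltration realized and 5) catheter malfunction". That section refers to Table 2, which has a column of operational definitions and a column of proposed benchmarks.

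The second IRRT row of Table 2 is called Treatment Time. Its definition is the bracketed difference "Delivered – Prescribed hours of dialysis therapy]/ Prescribed hours of dialysis therapy", with a benchmark of more than 85% of time. The third IRRT row, Solute Clearance, is the "Percentage difference between serum urea pre-treatment and serum urea post treatment".

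The only delivered-dose row in Table 2 is in the CRRT block: "Actual delivered dose in ml/Kg/h / Prescribed dose in ml/Kg/h". Its benchmark is above 85% of dose and between 25 and 30 ml/Kg/h. The same block has a separate time-based row, Downtime: "Time CRRT not running per day/ Each day of CRRT prescription".

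The section on KPI and interrupted time series analysis says that each KPI is analysed on its own and also in aggregate with the others.

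**The concern.** A primary outcome should have one name and one definition. Here the name says dose and the only definition in the matching position says hours. Two analysts working from the same article could produce different results for the same listed outcome. One would follow Table 2 and analyse the time delivered relative to the time prescribed. The other would follow the outcome list and look for a dose measure that the article does not give.

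What is at stake is the meaning of one reported result. A change in treatment hours reported under the label of delivered dose would claim more than was measured. Because each KPI is analysed separately, the item has its own analysis and also enters the aggregate.

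The KPI reports are also part of the intervention. The Methods/design section says: "Through this feedback the team members will work on adjusting and improving KRT practices that do not meet KPI benchmarks". If the sponsor intends a dose measure distinct from treatment time, units would receive a KPI for which this article sets no benchmark. That consequence depends on which measure is intended.

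**Working it through.** No power or sample-size figure is involved. The check is a row-by-row comparison, followed by a short calculation on the Treatment Time formula because it bears on the fix.

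**1. Names in the lists against rows in Table 2**

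| Item | Continuous: list | Continuous: Table 2 | Intermittent: list | Intermittent: Table 2 |
|---|---|---|---|---|
| 1 | filter life | Filter Life | treatment completion | Treatment Completion |
| 2 | downtime | Downtime | **delivered dose** | **Treatment Time** |
| 3 | delivered dose | Delivered Dose | solute clearance | Solute Clearance |
| 4 | ultrafiltration realized | Ultrafiltration Realized | ultrafiltration realized | Ultrafiltration Realized |
| 5 | access alarms | Access Alarms | catheter malfunction | Catheter Malfunction |

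Matches: continuous 5 of 5, intermittent 4 of 5, total 9 of 10. The lists and the table blocks are complete at five items each, so this is not a row lost in reading the PDF.

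**2. Can another row supply the missing dose definition?**

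- Solute Clearance cannot. It is item 3 in the lists and has its own row, so it is not also item 2.
- The CRRT Delivered Dose row cannot be carried over on the document's own terms. It is in the continuous block and its 25 to 30 ml/Kg/h target is given there.
- Treatment Time contains hours only. Nothing in the article says that it stands for intermittent dose.

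**3. Does the article use time and dose as one concept?** It does not. For continuous therapy, Table 2 has one row for time (Downtime) and another for Delivered Dose. Table 4 also lists time lost and dose as separate entries: "CRRT and IRRT data - filter life, reasons for retiring filters, treatment time lost, prescription/dose".

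**4. Share of the primary outcomes.** 5 continuous KPIs + 5 intermittent KPIs + 3 others (appropriate initiations, patients entering maintenance KRT, costs) = 13. Affected: 1/13 = 7.7%.

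**5. The Treatment Time formula against its benchmark.** The article gives no prescribed duration, so assume 4 h for illustration. As written, the value is (delivered − prescribed)/prescribed.

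- Fully delivered run: (4.0 − 4.0)/4.0 = 0%.
- Run delivered at 85% of prescription: (3.4 − 4.0)/4.0 = −15%.
- To exceed +85%: delivered > 4.0 × 1.85 = 7.4 h.

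The result does not depend on the assumed 4 h, since the formula equals delivered/prescribed − 1 for any prescription. With the plain ratio, the same runs score 4.0/4.0 = 100% and 3.4/4.0 = 85%, which is the scale of the stated benchmark. The mismatch between name and definition does not rest on this calculation. It shows that renaming the item without rewriting the row would leave a definition that does not fit its benchmark.

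**The case against.** The strongest reply is that this is a label slip in a condensed article. Nine of ten KPIs match, item 2 occupies the same slot in both places, and Treatment Time has a definition and a benchmark of its own. Read that way, the sponsor probably meant treatment time and no one would be misled for long. That argument fairly limits the severity. It does not remove the inconsistency: delivered dose is written in two separate sections, the article distinguishes time from dose elsewhere, and it nowhere says that one stands for the other.

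A second reply is that the full protocol may define intermittent dose. It may, so nothing here says that the trial has no definition. But this article chose to define its KPIs in Table 2, and its outcome list contradicts that table. That is more than a detail left to another document.

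A reader might infer three stronger points, which the article does not support:

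- *That the absence of a unit is the fault.* The CRRT Delivered Dose definition divides ml/Kg/h by ml/Kg/h, so it is unitless too. The fault is that the row measures hours and not dose.
- *That units will be asked to act on a KPI with no benchmark.* This holds only if a separate dose measure is intended. If Treatment Time is intended, a benchmark exists.
- *That Treatment Time is certainly right and the text wrong.* The article does not settle this. The text says dose twice, and Table 4 has a dose entry under a heading that covers both therapies. That entry is pooled, however, and does not show that delivered and prescribed dose are captured for intermittent runs.

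**Conclusion.** The point holds as an internal inconsistency. Intermittent delivered dose is a named primary outcome, Table 2 has no such row, and the row in its place measures hours. The scope is 1 of 10 KPIs and 1 of 13 primary items. The article gives no figures from which an effect on the results could be worked out, and none is claimed.

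The consequence depends on intent. If treatment time is the outcome, the label is wrong and the result cannot support a statement about dose. If dose is the outcome, this article leaves it without a definition or benchmark. Severity is low. It is a disagreement between text and table and does not call the choice of design into question. The conclusion rests only on comparing the outcome and report lists with Table 2, and Table 4 bears it out.

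**What to change.** Before data are analysed, the sponsor should state which measure is the second IKRT outcome and bring text and table into line, by one of two routes.

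(a) *Treatment time is intended.* Rename item 2 in the Primary outcomes list and in the list of report contents. Rewrite the Table 2 row as delivered hours divided by prescribed hours, so that it fits the existing benchmark of more than 85% of time. Do not describe the result as delivered dose. The cost is a change of wording in two places and one corrected formula, with no new kind of measurement.

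(b) *Dose is intended.* First confirm that delivered and prescribed dose are both captured for intermittent runs. Then keep the name and add an IRRT row to Table 2 with an explicit dose measure, unit and benchmark. State whether Treatment Time remains as an additional KPI. This costs more, because it depends on data that the article does not show to be available.

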### Secondary outcomes

Length of KRTICU and hospital lengths of stayICU and 90-day mortalityRates of KRT dependence at 90 daysHealth-related quality of life measurement (i.e., EQ-5D-5L and PedsQL) and patient-related outcome measures (PROMs) (i.e., ESAS-r and IPOS-renal)

### Data management

Effects of prescriber and acute KRT program patterns in the initiation of acute KRT will be determined by monitoring resource use associated with initiation of KRT at both a program level and healthcare system level. This will be done by determining first the units of each resource and then by assigning costs to each unit. At the program level we will capture the number of acute KRT initiations as well as total patient-days of acute KRT per specific modality (i.e., intermittent or continuous). These acute KRT initiations will also be adjusted for severity of illness to enable translation across units with varying case-mix, acuity and workload. Acute KRT disposable costs will include KRT filters, catheters, replacement and anticoagulation solutions.

New intake of critically ill survivors with severe AKI into ESKD dialysis programs will be reviewed on a quarterly and yearly basis to determine any changes relevant to use of this resource to the Alberta healthcare system. We will ensure that any changes in intakes reflect acute KRT initiations based on adherence to best-evidence practices.

Data will be collected on patient characteristics: (i.e., demographics, type of admission [medical, surgical, trauma]), clinical status (i.e., comorbid diseases including chronic kidney disease, primary diagnosis), acuity (i.e., APACHE II, SOFA, CFS), ICU treatment (i.e., duration of renal replacement therapy, mechanical ventilation, vasoactive therapy), ICU and hospital lengths of stay, and outcomes (i.e., renal recovery and mortality); and KRT-associated resource data: (i.e., filter use, prescription/dose, machine alarms/down time, anticoagulation, re-hospitalizations, progression of renal disease). Data variables to be captured are summarized in Table 4.

**Table 4 Tab4:** Data variables

Data Variable	Description
ICU location	admission ICU
Age	years
Sex:	M/F
Weight	kg
Date of Hospital Admission	dd/mm/yyyy
Date of ICU Admission (dd/mm/yyyy):	dd/mm/yyyy
Admission class	med/surg/neuro/trauma
ICU discharge location	unit/hospital
ICU Admission Diagnosis – cardiovascular, respiratory, gastrointestinal, genitourinary/renal, endocrinological/metabolic, neurological, trauma, burn, sepsis, surgery	yes/no
Co-morbidities – AIDS, chronic RRT, chronic heart failure, respiratory insufficiency, cirrhosis, diabetes mellitus, hepatic failure, immune suppression, leukemia, lymphoma, metastatic cancer, coronary artery disease	yes/no
Clinical Frailty Scale	number
APACHE II Score	number
SOFA score	number
Invasive/non-invasive ventilation	hrs/min
Vasopressors (include type)	hrs/min
CRRT/IHD/SLED	hrs/min
Cumulative daily fluid balance prior to RRT	mls
Creatinine, urea, pH, bicarbonate, potassium on day of RRT initiation	result
Renal Recovery at ICU Discharge	y/n - IHD
Renal Recovery at Hospital Discharge	y/n – IHD/PD
Renal Recovery at 6 Months	y/n - IHD/PD
ICU Mortality	A/D
Hospital Mortality	A/D
6-month Mortality	A/D
ICU length of Stay	days
Hospital Length of Stay	days
Number of admissions to site	aggregate
Patient days	aggregate
Ventilator days	aggregate
RRT days	Days CRRT/IHD/SLED
CRRT and IRRT data - filter life, reasons for retiring filters, treatment time lost, prescription/dose, machine alarms, machine down times, type of coagulation, blood flow rates, filtration fraction, adverse events, solute clearance, ultrafiltration realized	aggregate
Economic data - cost of filters, fluids, anticoagulation medications, RRT catheters, patient life-years gained, quality of life adjusted years (QUALY), re-hospitalizations, recurrence/chronic RRT, health care provider related costs	aggregate
QOL and PROMs	aggregate

Data sources will include multiple Alberta Health Services administrative databases, the Nephrology Information System (NIS) and the Patient Based Renal Information System (PARIS) (Supplementary Table 1) [20, 21].

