### Statistical analyses

#### Health outcome measures

The patients’ characteristics and the target clinic outcomes in the baseline and intervention periods will be summarized. Mean (SD) and/or median (IQR) will be used for continuous variable; frequency will be used for categorical variables. To compare pre- and post-intervention difference, *p*-values will be provided by t-test (for normally distributed variables), non-parametric Wilcoxon tests (for non-normally distributed variables) or Chi-square test (for categorical variables). Interrupted time series (ITS) analyses will use autoregressive integrated moving average (ARIMA) models to determine changes in the KPI performance following the implementation of the acute KRT pathway.

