#### KPI and interrupted time series analysis

Interrupted time series (ITS) analyses will be done using autoregressive integrated moving average (ARIMA) models to account for temporal trends and to determine whether there were changes in the process and clinical outcomes at the intervention period (compared with the baseline period) associated with implementation of the evidence-based acute KRT pathway. Each KPI will be assessed separately, as well as in aggregate with other KPIs. Autocorrelation, partial autocorrelation, and inverse autocorrelation functions will be assessed for model parameter appropriateness and seasonality. Stationarity will be assessed using the autocorrelation function and the augmented Dickey–Fuller test. The presence of ‘white noise’ was assessed by examining the autocorrelations at various lags, using the Ljung–Box χ2 statistic.

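### Before/after tests of mortality, length of stay and KRT dependence carry no case-mix adjustment, although severity is collected and adjustment is stated for KRT initiations

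*Protocol article*

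**What the plan says.** Four places in the protocol article bear on this.

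- **Data management.** Variation in case-mix is recognised, and severity adjustment is stated for one quantity, the count of acute KRT initiations: "These acute KRT initiations will also be adjusted for severity of illness to enable translation across units with varying case-mix, acuity and workload". The same section commits to collecting "acuity (i.e., APACHE II, SOFA, CFS") and "clinical status (i.e., comorbid diseases including chronic kidney disease, primary diagnosis"), together with admission type. Table 4 repeats the three scores, but its co-morbidity row shows chronic RRT and not chronic kidney disease.
- **Health outcome measures.** "The patients’ characteristics and the target clinic outcomes in the baseline and intervention periods will be summarized". The p-values for the pre/post difference then come from a t-test, a Wilcoxon test or a chi-square test, according to the type of variable.
- **KPI and interrupted time series analysis.** ARIMA models are used "to account for temporal trends and to determine whether there were changes in the process and clinical outcomes at the intervention period". No patient-level covariate is named.
- **Health-related quality of life and patient-reported outcome measures.** This is the one outcome model with a named covariate, and that covariate is the baseline PROM score.

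ICU and 90-day mortality, lengths of stay and 90-day KRT dependence are secondary outcomes. The number of patients entering maintenance KRT programs is listed among the primary outcomes.

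**The concern.** The comparison is between patients treated before and after the pathway arrives. Roll-out to ICUs is a randomised stepped wedge, but patients are not individually randomised and no exclusion criteria apply. Nothing in the design makes the two sets of patients alike in severity.

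There is also a specific reason to expect a difference. The analysed population is patients who receive acute KRT, and the prescriber reports are meant to change which patients are started. If the reports work, the severity of those who reach KRT may change at the same moment as the intervention. Crude mortality, stay or KRT dependence could then move in either direction with no effect of the pathway on any given patient.

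The plan collects the data needed to deal with much of this, but does not say that they will be used for these outcomes.

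**Working it through.** **1. Search for adjustment.** The document gives no sample size, power or event rate for these outcomes, so there is no figure to reproduce. The sections from Data management to Subgroup analysis were read for any use of severity, frailty or chronic kidney disease in an outcome analysis.

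| Section | Quantity analysed | Case-mix term stated |
|---|---|---|
| Data management | KRT initiations | Severity of illness |
| Health outcome measures | Clinical outcomes, pre/post | None; the tests named take no covariate |
| KPI and interrupted time series analysis | Process and clinical outcomes | None; time structure only |
| Patient-reported outcome measures | PROM scores | Baseline score only |
| Subgroup analysis | Primary and secondary outcomes | Age group, sex, ICU type and KRT volume as subgroups; no severity term |

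**2. Illustration of size.** Suppose the pathway has no effect, and mean APACHE II differs by *s* points between periods.

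Inputs:
- n = 1278 per period. This is the 2019 count in the Background; its use as the size of each period is an assumption.
- Assumed, not in the document: mortality p0 = 0.40, APACHE II SD 8, log-odds of death b = 0.05 to 0.10 per point, independent patients, two-sided 5% test.

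Formulae, with X normal, mean 0 and SD 8:
- Choose *a* so that the mean of expit(a + bX) is 0.40.
- p1 = mean of expit(a + b(X + s)); d = p1 − p0; p̄ = (p0 + p1)/2.
- se0 = √[2p̄(1 − p̄)/n]; se1 = √[(p0(1 − p0) + p1(1 − p1))/n].
- Rejection rate = Φ[(d − 1.96·se0)/se1] + Φ[(−d − 1.96·se0)/se1].

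Worked case, b = 0.10 and s = 1: a = −0.462, p1 = 0.4213, d = 0.0213, se0 ≈ se1 ≈ 0.01946. The first term is Φ[(0.0213 − 0.0381)/0.01946] = Φ(−0.87) ≈ 0.193 and the second is about 0.001, giving 0.194.

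| Shift s | b | p1 | False difference (points) | Type I error |
|---|---|---|---|---|
| 0 | either | 0.4000 | 0 | 5% |
| 1 | 0.05 | 0.4116 | 1.16 | 9.2% |
| 1 | 0.10 | 0.4213 | 2.13 | 19.4% |
| 2 | 0.05 | 0.4233 | 2.33 | 22.4% |
| 2 | 0.10 | 0.4428 | 4.28 | 59% |

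With baseline mortality varied from 30% to 50%, the range is about 9–20% for a 1-point shift and 21–60% for a 2-point shift.

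These rates apply to the chi-square comparison of two periods. They do not describe the ARIMA analysis.

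**3. Chronic kidney disease.** The Data management text promises "comorbid diseases including chronic kidney disease" and then says that the variables are summarised in Table 4. The co-morbidity row there has chronic RRT, which is a narrower category. The two lists do not match.

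**The case against.** **Silence is not refusal.** The article does not say that the other outcomes will go unadjusted, and covariate lists are commonly left to a statistical analysis plan. This stands for the ARIMA section, where the absence of a case-mix term proves little by itself. It does not stand for the pre/post comparison: the article names the tests that give the p-values, and those tests cannot take covariates.

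**The time series may be the real estimate of effect.** ARIMA also covers clinical outcomes and addresses temporal trends, so a gradual drift in severity can be partly absorbed. This stands, and the point is strongest for the pre/post tests. A shift that arrives with implementation is not absorbed, because it has the same timing as the effect being estimated.

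**The design and subgroups help.** The order of roll-out is randomised, and the subgroups separate adults from children and one ICU type from another. Neither balances severity between the patients treated before and after.

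**Stronger readings that the documents do not support.**
- A reader might infer that chronic kidney disease will not be available. The text commits to collecting it and renal information systems are among the sources, so a summary row shows only a mismatch.
- A reader might infer a large gain in power from adjustment. The usual 1 − ρ² variance reduction belongs to linear models and does not carry over to logistic models of mortality, KRT dependence or maintenance entry. The log-odds assumed above also imply a correlation between APACHE II and death of only about 0.19 to 0.35 at 40% mortality. No precision gain is claimed for the binary outcomes.
- A reader might infer that bias has been shown. The document gives no information on any actual shift; the risk is real but its size is unknown.

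**Conclusion.** The concern holds in limited form. The plan fixes covariate-free tests for the before/after comparison of clinical outcomes, names no case-mix term for ARIMA, and states severity adjustment for KRT initiations alone. In a comparison without individual randomisation, of a pathway that targets who starts KRT, a coincident change in severity would be counted as a pathway effect.

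Under the assumptions listed, type I error in the chi-square test for mortality rises from 5% to 9–19% for a 1-point APACHE II shift and to 22–59% for a 2-point shift. Only the 2019 volume comes from the document. The figures illustrate sensitivity and do not predict the trial's error rate.

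The plan should be changed on this point, since a better method is available from data that are already planned.

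**What to change.** - State that the t-test, Wilcoxon and chi-square comparisons are descriptive.
- Base inference for mortality, 90-day KRT dependence, maintenance-KRT entry and lengths of stay on patient-level regression that keeps ICU and calendar time and adds covariates fixed at ICU admission. For adults these are age, admission class, APACHE II, SOFA, Clinical Frailty Scale and pre-existing chronic kidney disease. Model the pediatric units separately.
- Do not adjust for values measured at the start of KRT, because the pathway may change them.
- Add chronic kidney disease to the Table 4 co-morbidity row so that it agrees with the Data management text.
- State that adjustment reduces, but does not remove, selection into the KRT-treated sample.

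The cost is model wording and one table entry for a variable already named in the text. The small downside is that missing scores need a stated handling rule.
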